#### Secondary analyses

The difference between the treatment groups in the proportions of patients with satisfactory relief of IBS symptoms at 12 weeks post-randomisation will be analysed using logistic regression models, adjusting for minimisation, baseline values, age, and gender. Odds ratios and corresponding 95% confidence intervals will be presented. Any missing data will be assumed MAR and imputed.

The differences between the two treatment groups in the continuous secondary endpoints at 12 weeks post-randomisation will be analysed using linear regression models, adjusted for the minimisation variables, baseline values where applicable, age, and gender. These endpoints are urgency of defaecation over the last month, stool frequency over the last month, number of days per week with at least one loose stool (BSFS > 5) over the last month, average stool consistency, number of days rescue medication used over 12 weeks, abdominal pain score, HADS depression and anxiety scores, SF-LDQ score, IBS-QOL score and subscales, and PHQ-12 and IBS-SSS severity scores. Treatment estimates and corresponding 95% confidence intervals will be reported. Any missing data will be assumed MAR.

The differences between the treatment groups in stool frequency, abdominal pain, and urgency of defaecation post-treatment, over weeks 13–16 post-randomisation, will be analysed using a linear regression model adjusted for minimisation factors, baseline values, and relevant baseline factors. Treatment estimates and corresponding 95% confidence intervals will be reported. Any missing data will be assumed MAR.

Exploratory analyses on the daily measurements (worst abdominal pain, loose stools, number of stools passed, consistency of stool, worst urgency, and use of loperamide) will be carried out using repeated measures models, which incorporate correlation between measurements from the same patient. SAS software version 9.4 will be used in the analyses of primary and secondary endpoints.

#### Safety analyses

All patients who receive at least one dose of trial treatment will be included in the safety analysis set. The number of patients reporting a SAE (up to 28 days after the last dose of treatment) and details of all SAEs will be reported for each treatment group. The number of patients withdrawing from trial treatment will be summarised by treatment arm, along with reasons for withdrawal. All safety analyses performed prior to final analysis will be undertaken by the safety statistician (rather than the trial statistician), thus ensuring that the trial team remain blinded.

#### Subgroup analyses

No subgroup analyses are planned.

#### Mechanistic studies

Mechanistic studies will be analysed blinded to the intervention allocation, by the site research fellow under supervision of the Chief investigator and local supervising PIs. The differences between treatment groups in changes in whole gut transit times, colonic motility measures (percent time of cyclical retrograde contractions and high-amplitude propagating contraction (HAPC) frequency), rectal compliance, and thresholds for urgency and pain measured using the barostat, faecal bile acid concentrations, and faecal tryptase will each be assessed by linear regression models. In addition, exploratory mediator analyses will explore whether treatment effects, in terms of changes in urgency or pain, are mediated through changes in faecal bile acids or protease. Exploratory subgroup analysis (tests of interactions) will be performed to investigate the effect of the presence of each specified single nucleotide polymorphism allele on response to treatment, using logistic regression with addition of an interaction term for the allele and treatment.

### Adverse events

An AE is any untoward medical occurrence (including deterioration of a pre-existing medical condition) in a patient or clinical trial patient administered a medicinal product, and which does not necessarily have a causal relationship with this product. The occurrence of reportable AEs will be recorded at visits 4, 5, and 6. At each visit the research nurse will complete the AE checklist to determine if the patient has suffered with any of the expected AEs. Only the confirmation of occurrence and corresponding severity will be recorded.

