#### Dose titration

Since the optimum dose varies widely from 4 mg on alternate days up to 8 mg t.d.s., we will start all patients on 4 mg daily and after 2 days contact them to adjust the dose, thus avoiding the complication of constipation. If stool consistency remains loose, patients will be asked to increase their dose in 4-mg steps every 2 days up to the maximum of 8 mg t.d.s. If stools become hard or there is no bowel movement on day 2, they will be asked to stop the drug for 1 day and recommence at a lower dose changing from 4 mg daily to 4 mg on alternate days. If stools still remain hard or infrequent, patients will be asked to reduce their dosage to 4 mg every third day. Patients will discontinue the trial in the unlikely event that their stool remains hard even at this low dose.

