The patient will return 2 weeks later to confirm eligibility. The diary will confirm they have had stool consistency BSFS 6–7 for more than 2 days a week and do not have only BSFS 7 for 7 days per week, and a weekly average worst pain score ≥ 30. Patients who consent to the whole gut transit study will be dispensed Transit-Pellet capsules containing markers, and the abdominal x-ray appointment will be confirmed for the morning of visit 3. Patients will take the Transit-Pellet capsules for 6 days prior to visit 3. Patients who have consented to one or both mechanistic studies will have appointments arranged for baseline assessment prior to visit 3.

#### Visit 3

On visit 3, patients will undergo a pregnancy test if applicable, whole gut transit assessment by abdominal x-ray (if they have consented), rigid sigmoidoscopy (if they have consented), completion of baseline questionnaire booklet (including IBS-SSS, SF-LDQ, HADS, PHQ-12, and IBS-QOL questionnaires), and collection of stool, whole blood, and serum samples (if they have consented). Patients will then be randomised and given a 6-week patient diary and the trial medication in accordance with their blinded randomisation allocation. Patients will be asked to record the following on a daily basis: stool frequency, consistency of each stool, worst abdominal pain experienced that day, worst bowel movement urgency, number of trial medication capsules taken, and whether they have used loperamide that day. Every week the diary will ask whether they feel that they have had satisfactory relief from their IBS symptoms that week. If they agree, the patient will continue to receive two text messages each day for the next 6 weeks, asking if they have passed a stool of a consistency of 6 or 7 that day, and what their worst abdominal pain was that day.

During the first 2 weeks patients will be contacted every 2 days by the local site team to discuss bowel habit. The dose of ondansetron or placebo will then be titrated as required. Additional guidance on dose titration will be given to each trial site in a standard operating procedure, and to the patient in a dose titration instruction leaflet. A check for serious adverse events (SAEs) will be performed during each telephone call. The steady dose to be taken forward for the remainder of the trial will be confirmed in week 2, although this may be altered during the 12 weeks if required, to avoid constipation.

#### Visit 4

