Patients will return for their fourth visit at 6 weeks of the trial treatment period. Diaries will be collected, and the investigator will ask whether any reportable AEs have occurred since the last visit. A pregnancy test will be taken and concurrent medications will be reviewed to ensure these do not interfere with the trial medication. A further 6-week patient diary, trial medication, and Transit-Pellet capsules (for use 6 days prior to visit 5) will be dispensed. Patients who have consented to mechanistic studies will have appointments confirmed and these will take place between 8 and 11 weeks of treatment. Daily text messages will be sent for a further 6 weeks to those patients who agree.

#### Visit 5

Patients will return for visit 5 after 12 weeks on the trial medication. A pregnancy test will be taken, concurrent medication will be reviewed to ensure that these do not interfere with the trial medication, and the investigator will ask whether any reportable AEs have occurred since the last visit. Unused medication and completed patient diaries will be collected. The abdominal x-ray to assess whole gut transit will be performed in consenting patients. Serum and stool samples will be collected from consenting patients, and all patients will complete the 12-week questionnaire booklet, including the IBS-SSS, SF-LDQ, HADS, and IBS-QOL questionnaires. Patients will be issued with a follow up diary and will continue to respond to text messages for a further 4 weeks.

#### Visit 6

Patients will then return for the sixth and final visit, where the diary will be collected and the investigator will ask whether any reportable AEs have occurred since the last visit.

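### Minor: non-serious constipation during titration first reaches the AE record at week 6, undated; a dated item on the existing calls would capture it better

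*Protocol article*

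**What the plan says.** Under Adverse events: "The occurrence of reportable AEs will be recorded at visits 4, 5, and 6". A research nurse completes a checklist of expected events at each visit, and "Only the confirmation of occurrence and corresponding severity will be recorded".

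Under Participant timeline, visit 3 is randomisation and the start of treatment. Visit 4 follows at 6 weeks: "Diaries will be collected, and the investigator will ask whether any reportable AEs have occurred since the last visit".

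Between these two visits the same section provides frequent contact: "During the first 2 weeks patients will be contacted every 2 days by the local site team to discuss bowel habit". The safety content it names for that contact is limited: "A check for serious adverse events (SAEs) will be performed during each telephone call". A steady dose is confirmed in week 2, "although this may be altered during the 12 weeks if required, to avoid constipation".

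Dose titration gives the purpose of the schedule, "thus avoiding the complication of constipation", and an exit rule for patients who cannot tolerate 4 mg every third day: "Patients will discontinue the trial in the unlikely event that their stool remains hard even at this low dose".

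Two other sources bear on the point. The daily diary (Participant timeline, visit 3) records stool frequency, the form of each stool and the capsules taken. Safety analyses plans a summary of treatment withdrawals by arm, with reasons.

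**The concern.** Safety is part of the primary objective (Objectives), and constipation is the side effect that titration is meant to prevent. For a titrated drug, prescribers will want to know whether constipation belongs to dose-finding or continues on the chosen dose.

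As described, the AE record cannot answer this for the first 6 weeks. A constipation report at visit 4 may come from any day since randomisation, and no date is kept. Staff who speak to the patient every other day about bowel habit obtain the relevant information, but the article describes no route from those calls to the AE record unless the event is serious. A patient who leaves under the exit rule may do so before the first visit at which the checklist is due.

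At stake is the completeness and usefulness of the constipation result, not the efficacy result.

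**Working it through.** No figure in the plan is contested, so the check is of the schedule.

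**Inputs**
- Titration: first 2 weeks, days 1 to 14 (Trial design; Dose titration).
- Calls: every 2 days in those 2 weeks (Participant timeline, visit 3).
- First AE checklist: visit 4, at 6 weeks, taken as day 42 (Participant timeline, visit 4; Adverse events).
- Look-back at visit 4: since visit 3, which is randomisation.
- Content recorded: occurrence and severity only.

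**Arithmetic**
- Share of the visit 4 window that is titration: 14 / 42 = 33%.
- Calls in titration: 14 / 2 = 7, none with a named check for non-serious events.
- Delay from an event on the last day of titration to the first AE question: 42 − 14 = 28 days.
- Delay from an event on day 1: 42 − 1 = 41 days.
- Recall period for titration events: 28 to 41 days, about 4 to 6 weeks.

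**What each source holds on constipation in weeks 1 to 6**

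| Source | Dated? | Limit |
|---|---|---|
| AE checklist, visit 4 | No | One answer for 42 days |
| Titration calls | Yes, by call | Only an SAE check is named |
| Daily diary | Yes, with capsules taken | Symptom data; collection is described at scheduled visits |
| Text messages | Yes, daily | Optional; ask only about loose stools and worst pain |
| Withdrawal summary | Not stated | Counts leavers and gives reasons |

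Only the first AE window is mixed. Visit 5 covers weeks 6 to 12 and visit 6 covers the 4 weeks after treatment; both begin after initial titration.

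**What cannot be calculated.** Dose titration does not say how long a patient stays on each reduced dose, so the day of exit cannot be derived. The number who take that path is not given either; the section calls it unlikely. The two constipation rates in the article are 2% in the pilot with titration and one quarter at a standard dose. Both are incidences of constipation, not of early exit, so neither gives the size of an under-count.

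**The case against.** The strongest reply is that the information already exists. The diary gives dated stool form beside dated capsule counts, which is finer than an onset date taken by telephone. Secondary analyses plans exploratory repeated-measures models of daily stool number and consistency. Constipation that persists beyond week 6 would be picked up separately at visit 5. Those who leave are counted with a reason. Recording occurrence and severity alone is an explicit choice for a drug with a long safety record. Most of this stands, and it is why the point is minor.

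Three stronger readings are tempting, and the article supports none of them.
- *The timing of early constipation is lost.* It is not; the diary largely recovers it.
- *Patients who leave for hard stools are missed.* The article describes no AE check at withdrawal, but it condenses a full protocol that is not shown and that may contain one. They are in any case counted among withdrawals.
- *Non-serious AEs will not be analysed, because Safety analyses names only SAEs and withdrawals.* Tabulation of non-serious events normally belongs in the SAP.

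A practical objection also has force. Hard stools, or no stool by day 2, are the signal for lowering the dose. Logging every such signal would turn planned dose adjustments into adverse events, so the item needs a threshold.

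What the reply leaves standing is the stated rule: the first AE question comes at week 6, the answer carries no date, and the calls carry only an SAE check.

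**Conclusion.** The point holds as a small, inexpensive improvement to safety recording. It is neither an error nor a contradiction. On the stated schedule, non-serious constipation in titration is first asked about for the AE record 28 to 41 days later, in one undated answer of which titration makes up 33% of the days. The AE record may therefore under-capture early constipation through recall and, possibly, through exits before visit 4. The size of any under-count is unknown.

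This rests on two assumptions. Constipation is taken to be on the checklist of expected events; the article does not print that list, though Investigational agent names constipation as a side effect. The early-exit part also requires that the full protocol has no AE check at withdrawal. The recall and dating part stands without that second assumption.

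Serious constipation is outside the point, because the calls check for SAEs. The recording procedure is the same in both blinded arms, and the primary endpoint, sample size and power are unaffected.

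**What to change.** 1. In Participant timeline (visit 3) and Adverse events, add a constipation item with onset date and severity to the existing titration calls. Set a threshold above the routine trigger for a one-day pause and a lower dose, so that ordinary titration signals are not counted as events.
2. In Adverse events, require the AE checklist at any discontinuation before visit 4, unless the full protocol already does so.
3. As a supporting measure, use the existing diary to report by arm the days with BSFS 1–2 stools or with no stool, for weeks 1–2 and weeks 3–12. Describe the split as calendar time, not as titration against stable dose, because the dose may still change after week 2.

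The cost is slightly longer calls by the same staff, a small CRF change and one derived diary variable. No new visit, staff or procedure is needed. Recorded constipation rates may be higher, which should be expected when they are compared with other trials.

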### Committees

#### Trial Management Group

A Trial Management Group (TMG) will be convened including the Chief Investigator, co-investigators and identified key collaborators, the trial statistician, and trial manager. Notwithstanding the legal obligations of the Sponsor and Chief Investigator, the TMG will have operational responsibility for the conduct of the trial. The TMG will meet quarterly as a minimum, and will be responsible for protocol completion, case report form (CRF) development, and monitoring of screening, recruitment, treatment, and follow-up procedures.

#### Data Monitoring and Ethics Committee

A DMEC will be convened to monitor data collected during the trial and make recommendations to the Trial Steering Committee (TSC) on whether there are any ethical or safety reasons as to why the trial should not continue. It will consist of an independent Chair, an independent statistician, and an independent clinician.

#### Trial Steering Committee

A TSC will be convened with an independent majority. Participants will include as a minimum, an independent Chair, an independent statistician, an independent clinician, a patient and public involvement (PPI) representative, the Chief Investigator, the Sponsor’s representative, and other members of the TMG as required to update on trial progress. The role of the TSC will be to provide overall supervision of the trial progress and advice on operational issues as necessary to the TMG. The TSC will meet annually as a minimum.

## Discussion

Our pilot study has shown that ondansetron provides an opportunity to help patients with IBS-D, not only with diarrhoea, but also with urgency, frequency of defecation, and bloating. When patients with IBS-D are asked about their concerns, erratic unpredictable bowel habit and urgency in particular, are rated as having the greatest impact on quality of life, so improvement in urgency and stool frequency may be of considerable value. However, abdominal pain is a key part of IBS, so we have used the combined FDA-recommended outcome measure, which includes both reduction in pain and improvement of diarrhoea as our primary endpoint, rather than just stool consistency, as in the pilot.

This larger clinical trial aims to confirm the effectiveness of ondansetron in managing IBS-D and, by mechanistic assessments, shed light on both the pathophysiology of the condition and the mode of action of ondansetron in this population. With greater understanding of the condition, we hope this will allow the design of better treatments in the future.

Current alternatives to 5HT3RA include loperamide and the recently introduced eluxadoline. There are only a few very small trials of loperamide in IBS-D, which clearly show its effectiveness in controlling diarrhoea but not pain [31, 32]. Anecdotally, patients often report constipation following loperamide use, and this is associated with bloating and discomfort. Eluxadoline is a combined μ-opioid agonist and δ-opioid antagonist shown to increase the proportion of responders from 5.7% on placebo to 11–13.8% in a dose-response study [33]. However, the main effect was on stool consistency with no obvious effect on pain. Unfortunately, this drug has been associated with acute pancreatitis, which is an unacceptable side effect for most patients with IBS so the search for alternative safe treatments remains important.

If ondansetron is effective in our trial, it could easily be widely adopted since it is an inexpensive, safe, and generic drug. By providing an effective treatment, it could not only reduce patient symptoms, but also reduce healthcare costs associated with repeated referral and unnecessary investigations.

### Protocol version

Protocol version 6.0, 6 November 2018 amended 5 December 2018. Recruitment opened on 19 March 2018, expected completion December 2021.

## Data Availability

Request for access to the data and any material will be considered by the TSC and the co-investigators.

## Abbreviations

5HT: 5-Hydroxytryptamine
5HT_3_RA: 5HT_3_ receptor antagonists
BSFS: Bristol Stool Form Score
CONSORT: Consolidated Standards of Reporting Trials
CTRU: Clinical Trials Research Unit
DMC: Data Monitoring Committee
ECG: Electrocardiogram
FDA: Food and Drug Administration
HADS: Hospital Anxiety and Depression Scale
HAPC: High-amplitude propagating contraction
HRM: High Resolution Manometry
IBS: Irritable bowel syndrome
IBS-D: Irritable bowel syndrome with diarrhoea
IBS-QOL: IBS Quality of Life Questionnaire
IBS-SSS: IBS Severity Scoring System
IMP: Investigational medicinal product
mg: Milligrams
ml: Millilitres
PAR2: Protease activated receptor 2
PHQ-12: Patient Health Questionnaire
PI: Principal Investigator
QT: Interval is the time from the start of the Q wave to the end of the T wave
QTc: Corrected QT
RCT: Randomised controlled trial
SAE: Serious adverse event
SeHCAT: Selenium homocholic acid taurine
SF-LDQ: Short-form Leeds Dyspepsia Questionnaire
t.d.s: Three times a day
TMG: Trial Management Group
TPH-1: Tryptophan hydroxylase 1
TSC: Trial Steering Committee
